### Assessments

#### Home assessments

During each dietary intervention, in addition to daily dietary recall, participants will be provided with study-specific morning and evening questionnaires to assess daily subjective measures of sleep, mood, and exercise activity. Further, at the end of each week, physical activity will be assessed [57].

##### Sleep, mood, and exercise questionnaires

For the duration of the study period, participants will be required to complete a customized sleep diary every morning (morning questionnaire) to assess perceived sleep quality as well as morning vigilance on two separate 100-mm Visual Analogue Scales (VAS), anchored from the “worst sleep” to the “best sleep ever,” and “not at all fresh and alert” to the “most fresh and alert ever,” respectively. The morning questionnaire will also provide information on each participant’s sleeping habits, such as what time they went to bed, how long they think it took them to fall asleep, and what time they woke up. Thus, information on each participant’s sleep-wake cycles can be retrieved. Each evening, throughout the study, participants will be required to complete a customized evening questionnaire to assess current mood on a 100-mm VAS anchored from “worst mood ever” to “best mood ever.” The evening questionnaire also asks for information on the type, duration, and intensity of any exercise performed during the day. At the end of each week, physical activity will be further assessed using the standardized GPAQ [57].

#### Laboratory assessments

Before and after each dietary intervention (i.e., four times), participants will return to the laboratory after an overnight fast, for anthropometric measurements and to provide a blood sample. Tests to assess cognitive function tests and BMR will also be assessed at each of these visits, and validated and standardized Pittsburgh Sleep Quality Index (PSQI) [55] questionnaires will be administered to assess sleep quality.

##### Anthropometry

Height (to the nearest centimeter) and body mass (to the nearest 100 g) will be measured using a stadiometer (Holtain Ltd., Crymych, UK) and electronic scale (Dismed, Miami, FL, USA) respectively. Participants will be measured without shoes and while wearing light clothing. Biceps, triceps, supra-iliac and sub-scapularis skinfolds (to the nearest 2 mm) using Holtain skinfold calipers (Holtain Ltd., Crymych UK), will be used to determine body fat percentage of each participant [58].

##### Cognitive function

Cognitive function will be assessed using a battery of computerized cognitive tests (Cogstate computerized tests (www.cogstate.com)) performed on a laptop computer with headphones. In order to avoid a learning effect of performing these cognitive function tests, participants will be required to perform the battery of tests and repeat it three times during the habitual diet screening week. Cognitive tests will include: (1) Groton Maze learning task (to assess executive function), (2) Identification test (to assess attention), (3) Psychomotor vigilance task (to assess reaction times), (4) One-card learning task (to assess visual learning), and (5) Two-back test (to assess working memory). This battery of tests will be done during the habitual dietary screening week, as well as before and after each dietary intervention.

##### Blood sampling and collection

After an overnight fast (minimum of 10 h) a 10-ml venous blood sample will be drawn by venous puncture from the brachial vein of the participant for the assessment of biomarkers of cardiovascular and metabolic health. These biomarkers include lipid profiles (concentrations of triglycerides, LDL, HDL and total cholesterol), interleukin-6 (IL-6), interleukin-1 (IL-1), high-sensitivity C-reactive protein (hsCRP), tumor necrosis factor alpha (TNF-α), ferritin, and serum amyloid P. The blood sample will also be used to assess thyroid function by measuring levels of thyroid stimulating hormone (TSH), T3 and T4. Blood samples will be taken before and after both dietary interventions. Samples will be analyzed by a reputable external laboratory (Clinical Laboratory Service, Johannesburg, South Africa).

##### Basal metabolic rate

Basal metabolic rate will be measured using respiratory gas analysis via a computerized metabolic system (Quark ergo, COSMED, Rome, Italy). Participants will lie supine on a plinth for a period of 15 min with a face mask, covering their mouth and nose, connected to the metabolic system. Oxygen consumption, carbon dioxide production, ventilation, and respiratory rate will be recorded throughout the procedure. Average energy expenditure (kcal/min/kg) over the last five of the 15 min will then be recorded as BMR. The room temperature of the laboratory will be maintained at 27 °C for all participants.

### Outcomes

All outcomes will be measured at baseline, and before and after 3 weeks of each dietary intervention. The primary outcome will be diet-induced change in sleep quality, cognitive function, markers of inflammation and cardiovascular health status. The secondary outcomes will be a change in BMR and thyroid function.

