### Data analysis

Data analysis will be done using IBM SPSS Statistics (version 24, IBM Corporation, NY, USA). A two-tailed statistical significance will be accepted at *P* < 0.05. Each outcome variable assessed will be analyzed according to diet (KD or HCLF) and time (before and after each diet) using a repeated-measures two-way analysis of variance (ANOVA). Where appropriate, a Student-Newman-Keuls post-hoc test will be used to assess the origin of any significant differences detected by the ANOVA models. Variables will be adjusted for potential confounders which will be determined using multiple linear regressions. A power analysis has indicated that total of 20 participants would provide 85% power to obtain a medium effect size for BMR (Cohen’s *d* effect size = 0.3) [54].

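### The primary outcome is four domains holding at least 16 variables, each tested at two-sided 0.05 with no stated control across them

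*Protocol article*

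**What the plan says.** The Outcomes section of the protocol article defines one primary outcome that spans four domains: "The primary outcome will be diet-induced change in sleep quality, cognitive function, markers of inflammation and cardiovascular health status". BMR and thyroid function are secondary.

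The variables in those domains are listed under the assessments:

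- **Sleep quality.** Laboratory assessments: "validated and standardized Pittsburgh Sleep Quality Index (PSQI) [55] questionnaires will be administered to assess sleep quality". The home diary adds ratings "to assess perceived sleep quality as well as morning vigilance on two separate 100-mm Visual Analogue Scales (VAS").
- **Cognitive function.** The Cognitive function section lists five computerised tests, each tied to a different ability.
- **Inflammation and cardiovascular health.** Blood sampling and collection: "These biomarkers include lipid profiles", with four lipids named, followed by IL-6, IL-1, hsCRP, TNF-α, ferritin and serum amyloid P.

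The Data analysis section sets the level: "A two-tailed statistical significance will be accepted at *P* < 0.05". It then sets the unit of analysis: "Each outcome variable assessed will be analyzed according to diet (KD or HCLF) and time (before and after each diet"), by a two-way repeated-measures ANOVA. The only follow-up procedure is this: "Where appropriate, a Student-Newman-Keuls post-hoc test will be used to assess the origin of any significant differences detected by the ANOVA models".

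**The concern.** A primary outcome normally tells the reader in advance which result the trial's main conclusion rests on. Here the label covers four areas of physiology, each but sleep measured by several variables, and nothing ranks or combines them. Every variable is tested at the level that would suit a single primary test. No rule says how many variables, or which ones, must differ before an effect of the ketogenic diet is claimed.

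At stake is how a reader may take a primary finding. If one or two of these variables reach P < 0.05, they can be reported as primary results, although a result of that kind is quite likely when neither diet does anything. The article itself fixes the four-domain primary outcome and the per-variable testing at 0.05. This is therefore a fault in what is written, and not merely detail left to an analysis plan.

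**Working it through.** **Stated figure.** The article gives no overall error rate to reproduce. Its one design figure, 85% power with 20 participants, is for BMR, a secondary outcome, and does not enter this calculation.

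**Inputs from the article**

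| Domain | Variables | Count |
|---|---|---|
| Sleep quality | PSQI | 1 |
| Cognition | five computerised tests | 5 |
| Lipids | triglycerides, LDL, HDL, total cholesterol | 4 |
| Inflammatory and other markers | IL-6, IL-1, hsCRP, TNF-α, ferritin, serum amyloid P | 6 |
| Total | | 16 |

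This takes one score per questionnaire or test, so it is a minimum. The two morning scales would make 18. Level: 0.05 two-sided. Sample size: 20.

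**Assumptions.** No variable truly changes. One test per variable counts, namely diet by time, because the outcome is defined as diet-induced change. Correlations between variables are not given, so a range is used.

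**Independent tests.** The chance of at least one P < 0.05 among k tests is 1 − 0.95^k.

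- k = 16: 1 − 0.95^16 = 0.560
- k = 18: 1 − 0.95^18 = 0.603
- k = 10, a deliberately short list: 1 − 0.95^10 = 0.401
- k = 4, one per domain: 1 − 0.95^4 = 0.185

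**Correlated tests, k = 16, common correlation.** Two calculations agree closely. One treats the test statistics as normal. The other simulates t tests with n = 20.

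| Correlation | Normal | t tests, n = 20 |
|---|---|---|
| 0.2 | 52% | 52% |
| 0.3 | 48% | 48% |
| 0.5 | 37% | 39% |
| 0.7 | 26% | 28% |

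If variables correlate only within their own domain, at 0.3, 0.5 or 0.7, simulation gives 53%, 49% and 42%.

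**Student-Newman-Keuls.** It compares the diet-by-time cell means of one variable after that variable's ANOVA is significant. It never compares or pools P values from different variables, so it leaves all the figures above unchanged.

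**Effect of Holm on four tests.** Holm's first step uses 0.05/4 = 0.0125. For a within-person contrast with n = 20 (19 degrees of freedom) and 80% power, the noncentral t distribution gives a detectable standardised difference of 0.66 at 0.05 and 0.81 at 0.0125.

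**The case against.** The best reply is that the article never says one positive variable makes the trial positive. It asks separate questions about sleep, cognition and cardiovascular health, and results might be read domain by domain. That is correct. A reader might infer a success rule of at least one positive variable out of 16, but no section states it, and 56% is the error rate of that reading only. The reply does not remove the fault. The article states no narrower rule, and the mildest reading, one unadjusted variable per domain, still gives 18.5%.

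Second, multiplicity is often left to the analysis plan, and the article does not rule out adjustment. This stands in part: silence on adjustment alone would be no finding. But a later plan would have to choose among outcomes that this article already declares jointly primary.

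Third, three stronger readings are tempting and should not be made.

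- **About 91%.** This counts all three F tests per variable (1 − 0.95^48 = 0.915). A time main effect says nothing about one diet against the other, and diet-induced change corresponds to the diet-by-time test alone.
- **Student-Newman-Keuls as a cause.** The inflation comes from the 16 unadjusted tests. The procedure's own error over four means reaches about 10% in one configuration (two equal pairs) if any significant F test opens it. It is about 3% if a significant interaction is required, and the article does not say which applies.
- **18 variables.** One of the two morning scales rates alertness, which the article does not label sleep quality, so 16 is the safer count.

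Finally, the blood markers are unlikely to be independent, since total cholesterol moves with LDL and HDL. That is why a range is given and 56% is not offered as the single answer.

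**Conclusion.** The concern holds. The primary outcome is four domains with at least 16 variables and no lead variable, composite or order, each variable is tested at two-sided 0.05, and no control across them is stated. If nothing truly changes and one diet-by-time test per variable counts, at least one false-positive primary result has probability 56% under independence and about 26% to 52% for common correlations from 0.7 down to 0.2. Every value in that range is at least five times the nominal 5%.

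The count comes from the article. The correlations are assumed, and the rate applies to a claim based on any one of the variables. The article does not state such a claim as its rule, but nothing in it prevents one.

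**What to change.** 1. Name one primary variable in each of the four domains.
2. For each, make the between-diet difference in change (the diet-by-time contrast) the only confirmatory test.
3. Apply Holm across the four tests at an overall two-sided 5%.
4. Label all other variables secondary or exploratory, and report them with estimates and confidence intervals.
5. Base any primary conclusion on the contrast in step 2, and not on Student-Newman-Keuls comparisons of before and after within one diet.

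The choice needs care over timing. Trial status says that recruitment began in May 2017, and the Study design section says that the principal investigator, who collects the outcomes, is not blinded to diet. The four variables should therefore be chosen and dated before analysis by someone without access to outcome data by diet.

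A composite, a fixed testing order or an openly exploratory label would also answer the point. Holm over four is proposed because it keeps all four domains.

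**Cost.** A change of wording and a dated record, with no new data. At Holm's first step the standardised within-person difference detectable with 80% power at n = 20 rises from 0.66 to 0.81, so a real but moderate effect is easier to miss.

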### Data analysis

Data analysis will be done using IBM SPSS Statistics (version 24, IBM Corporation, NY, USA). A two-tailed statistical significance will be accepted at *P* < 0.05. Each outcome variable assessed will be analyzed according to diet (KD or HCLF) and time (before and after each diet) using a repeated-measures two-way analysis of variance (ANOVA). Where appropriate, a Student-Newman-Keuls post-hoc test will be used to assess the origin of any significant differences detected by the ANOVA models. Variables will be adjusted for potential confounders which will be determined using multiple linear regressions. A power analysis has indicated that total of 20 participants would provide 85% power to obtain a medium effect size for BMR (Cohen’s *d* effect size = 0.3) [54].

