## Methods

### Study design

The design of the study is a randomized controlled, cross-over trial. The study will follow the Standard Protocol Items: Recommendations for Interventional Trials (SPIRIT) guidelines for the design and conduct of a trial (Fig. 1; Additional file 1) [53]. As outlined in Fig. 2, participants will be asked to visit the Movement Physiology Research Laboratory on five occasions; the first visit will be for screening the volunteers to ensure that they fit the study criteria. Thereafter, eligible participants will return to the laboratory before the start of, and after, each dietary intervention. Following 1 week of normal habitual dietary monitoring, each participant will follow two isocaloric diets (a KD and a high-carbohydrate, low-fat (HCLF) diet) in a randomized order and separated by a 1-week washout period. Randomization of the order of the diets will be done using the Microsoft Excel 2010 (Version 14.0) CHOOSE and RANDBETWEEN functions. These functions (=CHOOSE(RANDBETWEEN(1,2), “A”,“B”) are able to assign each new participant into one of the two diets. Each dietary intervention will last for a minimum period of 3 weeks. In the KD it is critical for the participant to remain in a ketogenic state for three consecutive weeks. Should the participant leave the ketogenic state (as assessed by blood ketone levels), the dietary intervention period will be prolonged until the consecutive, 3-week ketogenic state is achieved. If a participant does not reach a ketogenic state in 2 weeks, we will exclude them, as it is indicative of non-compliance. However, we will be more lenient with someone who has entered a ketogenic state but may struggle to maintain the state, in which case we will guide them by closely monitoring their diet to ensure that their carbohydrate intake is suitably low and that their fat intake is suitably high. We will also look at the content of each participant’s diet to ensure that the foods do not contain imperceptible carbohydrates or that their protein content is not too high, which may result in gluconeogenesis. We will continuously encourage pure fat intake, e.g., cooking with olive oil, butter or coconut oil. Should a participant leave the ketogenic state more than five times they will be excluded from the study.

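### The diet × time ANOVA subtracts each period's baseline in full; adjusting for that baseline would usually be more precise, by an amount the documents do not fix

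*Protocol article*

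**What the plan says.** - **Model (Data analysis).** "Each outcome variable assessed will be analyzed according to diet (KD or HCLF) and time (before and after each diet"). The method named for this is a two-way ANOVA with repeated measures, and it applies to every outcome.
- **Target (Outcomes).** "The primary outcome will be diet-induced change in sleep quality, cognitive function, markers of inflammation and cardiovascular health status".
- **Measurements (Laboratory assessments).** "Before and after each dietary intervention (i.e., four times), participants will return to the laboratory after an overnight fast". Each period therefore has its own baseline.
- **Design (Study design).** The two diets are taken "in a randomized order and separated by a 1-week washout period".
- **Adjustment (Data analysis).** "Variables will be adjusted for potential confounders which will be determined using multiple linear regressions". The period baseline is not named as one of these variables.
- **Error rate and size (Data analysis).** "A two-tailed statistical significance will be accepted at *P* < 0.05"; a "total of 20 participants would provide 85% power to obtain a medium effect size for BMR", with Cohen's d given as 0.3.

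The article does not say which term of the ANOVA is the test of diet, and it states no correlation between visits and no within-person SD.

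**The concern.** In the stated model the before-diet value is one level of the time factor, so it is a response and not a covariate. The diet main effect averages the before visits, at which the coming diet has not yet acted, with the after visits. Only the interaction isolates a diet-induced change.

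The interaction takes the whole baseline off each post-diet value. In a parallel-group trial that can help, because it removes stable differences between people. Here each person already serves as their own control, so the stable part cancels when KD is compared with HCLF. What the two baselines then contribute is partly, and possibly only, visit-to-visit noise. Regression on the baseline difference lets the data decide how much to subtract.

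The trial plans 20 people. What is at stake is precision on every laboratory outcome, from measurements that will be collected in any case.

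**Working it through.** **The plan's own figure.** The article gives no variance for the diet contrast. Its only related figure is 85% power at d = 0.3 with 20 people. Read as a paired standardised difference, two-sided 0.05, that gives 24.7%, so the 85% is not reproduced on that reading. This is a separate matter and nothing below depends on it.

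**Step 1: what the interaction tests.** With two levels per factor and everyone measured in all four cells, the interaction F(1,19) is the square of the paired t for

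C = (KD after − KD before) − (HCLF after − HCLF before).

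A check on simulated data gave F = 0.7531 and t² = 0.7531.

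**Step 2: variances.** Per person, let P be the KD minus HCLF difference in post-diet values and B the same difference in period baselines. Assume equal variances V and correlation r. Then:

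- Planned contrast, C = P − B: variance 2V(1 − r).
- Post-diet values only, P: variance V.
- Baseline-adjusted, P regressed on B: variance V(1 − r²).
- Planned relative to adjusted: 2V(1 − r) / [V(1 − r²)] = 2/(1 + r).

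**Step 3: the diet main effect is no way out.** It is ½(P + B). Its expectation is half the diet effect and its variance is V(1 + r)/2. Rescaled to the full effect, the variance is 2V(1 + r). Relative to the adjusted analysis this is 2/(1 − r): again 2 at r = 0, and larger when r is positive.

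**Step 4: cost of the slope.** Estimating one slope inflates the adjusted variance on average by (n − 2)/(n − 3) = 18/17 at n = 20, so the ratio becomes [2/(1 + r)] × 17/18.

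| r (assumed) | Large sample, 2/(1+r) | n = 20, formula | n = 20, simulated |
|---|---|---|---|
| 0 | 2.00 | 1.89 | 1.89 |
| 0.3 | 1.54 | 1.45 | 1.46 |
| 0.5 | 1.33 | 1.26 | 1.28 |
| 0.7 | 1.18 | 1.11 | 1.11 |
| 0.9 | 1.05 | 0.99 | – |

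Simulated type I error was between 4.8% and 5.3% for both analyses. Adding a period term to the adjusted model changes little (simulated ratios 1.84, 1.44, 1.25 and 1.10 for the first four rows).

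**Step 5: r in terms of visit correlations.** If two visits in the same period correlate w and visits in different periods correlate b, then r = (w − b)/(1 − b).

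| w / b (assumed) | r | 2/(1+r) |
|---|---|---|
| equal | 0 | 2.00 |
| 0.8 / 0.7 | 0.33 | 1.50 |
| 0.8 / 0.6 | 0.50 | 1.33 |
| 0.9 / 0.7 | 0.67 | 1.20 |
| 0.9 / 0.6 | 0.75 | 1.14 |

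The gain shrinks when before and after values in one period agree much more closely than values from different periods.

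**Step 6: power.** With 20 people, 85% power in a paired test needs a standardised difference of about 0.707. Suppose the adjusted analysis achieves that. Dividing 0.707 by √[2/(1+r)] gives power for the planned test of 56%, 68%, 74% and 79% at r = 0, 0.3, 0.5 and 0.7. Using the n = 20 formula ratios instead gives 59%, 70%, 76% and 81%.

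**The case against.** **The planned test is valid and matches the stated outcome.** It tests change by diet, and change is what the Outcomes section names. Without carry-over it is unbiased and holds its error rate. This stands: the point is about efficiency only.

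**The article does not name the interaction, and an analysis plan might fix the contrast and covariates.** This stands in part. The article does state the model, however, and that model puts the baseline on the response side. The sentence on unnamed confounders does not move it.

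**The loss may be small.** This stands. At within/between-period correlations of 0.9/0.7 or 0.9/0.6 the large-sample ratio is only 1.20 or 1.14, before the slope cost. The documents give nothing to choose between these cases and r = 0.

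**Carry-over.** A reader might infer that, with one week of washout, full subtraction is also the more biased choice. The documents do not support that. Take an assumed residual of 0.3 SD after one of the diets, at the second before visit:

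- If it persists unchanged to the second after visit, change scores remove it, while ANCOVA is off by about 0.15 SD (r = 0) or 0.07 SD (r = 0.5).
- If it has gone by then, change scores are off by 0.15 SD and ANCOVA by 0 or 0.075 SD.

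Which analysis suffers more depends on how the residual decays, which is not given. Carry-over is therefore no argument for either analysis here.

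**Conclusion.** The point holds as one of precision. The term that answers the stated question subtracts each baseline in full, and its large-sample variance is 2/(1 + r) times that of a baseline-adjusted analysis of the same data. The algebra is exact given equal variances of the baseline and post-diet differences. The size for this trial is an assumption: about 1.9 to 1.1 at n = 20 for r from 0 to 0.7, and nothing or a slight loss near r = 1.

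Three stronger readings should be resisted:

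- That 20 people are made to act like 10. This is the large-sample limit at r = 0; with the slope estimated, the ratio there is about 1.9, and it falls as r rises.
- That the planned test gives false positives or bias. Its type I error is about 5%.
- That the visit spacing shows r to be low. That needs a model for how visits correlate over time, which the documents do not supply.

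The change is worth making because it is cheap, the sample is small and the same model serves every outcome.

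**What to change.** In Data analysis, replace the diet × time ANOVA as the test of diet with a cross-over ANCOVA. For each outcome, regress the within-person KD minus HCLF difference in post-diet values on the KD minus HCLF difference in period baselines, with a period term (diet order, in this difference form), or fit the equivalent mixed model. Take the diet effect at a baseline difference of zero, and report it as the adjusted KD minus HCLF difference with its 95% CI. State that the diet main effect of the ANOVA will not be used for conclusions about diet.

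The cost is a change of wording and one degree of freedom for the baseline slope. No new data are needed, since all four laboratory visits are already planned. The downside is a negligible gain, or a slight loss, for any outcome with r close to 1.

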**Fig. 2 Fig2:**
[figure not shown]
Timeline and details of study procedures

The principal investigator (PI) who is collecting the outcome measures will not be blinded to the diet allocation because feedback may need to be provided on a daily basis, to encourage dietary compliance. A researcher that will conduct the statistical analysis will, however, be blinded to the order in which the diets were undertaken.

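### The cross-over ANOVA has no period term, and blinding the analyst to diet order stops one being fitted as planned; the cost is a split-dependent bias and lost power if the before/after change differs between periods.

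*Protocol article*

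**What the plan says.** - Protocol article, Study design: "The design of the study is a randomized controlled, cross-over trial". There are two diets, taken in random order with a one-week washout. The order comes from a spreadsheet random draw; the functions "are able to assign each new participant into one of the two diets". No blocking or forced equal split is described.
- Study design, paragraph after Fig. 2: the researcher doing the statistics "will, however, be blinded to the order in which the diets were undertaken".
- Laboratory assessments: outcomes are measured at four visits, one before and one after each diet.
- Outcomes: "The primary outcome will be diet-induced change in sleep quality, cognitive function, markers of inflammation and cardiovascular health status".
- Data analysis: each outcome is "analyzed according to diet (KD or HCLF) and time (before and after each diet) using a repeated-measures two-way analysis of variance". On adjustment it adds: "Variables will be adjusted for potential confounders which will be determined using multiple linear regressions". Neither period nor sequence is named as a factor or covariate.

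**The concern.** Period is a design factor in a two-period cross-over. If participants change by a different amount during their first diet than during their second, whatever the diet, that difference enters each person's diet comparison with a sign set by their order. With equal sequence groups it averages out of the estimate but stays in the error term and widens the interval. With unequal groups part of it also stays in the estimate.

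Cognitive function is one of the primary outcomes, and the article itself recognises learning on those tests. If practice gains flatten over time, the before/after gain is larger in the first period than in the second. Incomplete return to habitual values after the washout would also alter the second-period change, even if equal for both diets. With 20 participants there is little precision to spare. The variable needed to remove the effect is the one withheld from the analyst.

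**Working it through.** **The plan's own figure.** The article gives no period-effect size. Its only related figure is 85% power with 20 participants at an effect size of 0.3. Read as a paired effect (two-sided 5%), 0.3 gives 24.7%, so the figure is not reproduced that way. That is a separate matter. I use 0.71 SD of the within-person difference as the true diet effect, because a paired test with n = 20 then has 85% power.

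**Set-up.** For participant i let D_i = (change on KD) − (change on HCLF), in units of its SD. With two within-person factors at two levels each, the diet × time test is the paired t-test on D (F = t², 19 error degrees of freedom). Write D_i = τ + p·s_i + e_i, where τ is the diet effect, s_i = +1 or −1 by sequence, and p is the period difference in the change.

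**What cancels.** If both visits of period 2 are shifted by a, the change is (after + a) − (before + a) = after − before. Such a level shift drops out of D. It remains only in the diet main effect, which averages over before and after.

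**Split.** With independent draws, n1 ~ Binomial(20, 0.5):
- P(10:10) = 17.6%, so P(unequal) = 100 − 17.6 = 82.4%
- P(13:7 or worse) = 26.3%
- P(14:6 or worse) = 11.5%

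**Bias given the split, no period term.** Bias = p(n1 − n2)/N:
- 12:8: 4/20 = 0.2p
- 13:7: 6/20 = 0.3p
- 14:6: 8/20 = 0.4p, so 0.20 SD when p = 0.5 SD

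**Type I error without a period term** (simulation; p is assumed):

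| Split | p = 0.25 | p = 0.5 | p = 1.0 |
|---|---|---|---|
| 10:10 | 4.4% | 2.9% | 0.6% |
| 12:8 | 4.9% | 4.5% | 3.0% |
| 13:7 | 5.5% | 6.7% | 7.5% |
| 14:6 | 6.4% | 9.8% | 16.6% |
| Averaged over allocation | 4.9% | 4.9% | 5.0% |

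With a period term the error is 5% at every split tried.

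**Power at τ = 0.71:**

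| p (SD) | No period term, 10:10 | No period term, averaged | Period term, averaged |
|---|---|---|---|
| 0 | 85.3% | 85.3% | 83.0% |
| 0.25 | 83.7% | 83.1% | 83.0% |
| 0.5 | 78.7% | 76.8% | 83.0% |
| 1.0 | 57.4% | 56.1% | 83.0% |

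With the period term, power does not depend on p. It is 85.1% at 10:10, 83.6% at 12:8, 81.6% at 13:7 and 78.5% at 14:6, and the estimate is unbiased throughout.

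**The case against.** The strongest reply is that this design already limits period effects. Each period has its own pre-diet measurement and the outcome is a change, so constant shifts cancel. Season, mask familiarity and reporting fatigue would act partly or mainly as such shifts. The cognitive battery is also rehearsed during the habitual week. All of this stands. It narrows the concern to period differences in the change, but does not exclude them.

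Second, simple randomisation is valid. Averaged over the draw, the unadjusted estimate is unbiased and the test keeps its level. A reader might infer from the 14:6 row that the trial's type I error is 10% to 17%. The documents do not support that: those figures are conditional on a split which, with anything worse, has probability 11.5%, and on assumed period effects of 0.5 to 1 SD. At 10:10 the test is conservative. The trial will nevertheless have one realised split, and its reported estimate carries that split's bias.

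Third, a reader might infer that a period effect can never be removed. That is true only of the plan as written; order is known to the trial and can be supplied. Nor does the article say that the analyst sees diet identity; it mentions only order.

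Fourth, the planned confounder adjustment might be thought to cover period. It cannot while the analyst lacks order. Nor is this a detail left to an analysis plan: the article names the model's factors and the blinding itself.

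**Conclusion.** The point holds in limited form. The stated model omits a basic factor of the design, and the stated blinding prevents its inclusion as planned. The consequence is a bias that depends on the realised split and, averaged over allocation, lost power; the randomised test itself remains valid. The power loss is about 85.3 − 76.8 = 8.5 points if the period effect on the change is 0.5 SD, about 2 points at 0.25 SD, where fitting the term costs the same, and none at zero. These sizes rest on an assumed period effect, since the documents give none, on a diet effect of 0.71 SD, on normal errors and on complete data from 20 participants. The change is cheap and uses data already held, so it is worth making, but it has to be fixed before the analysis.

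**What to change.** Before analysis, give the analyst period and a sequence code, and mask the diets as X and Y, with ketone values and diet records kept out of the analysis file. This keeps the analyst masked without withholding a design factor.

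Analyse the change in each period, or the post-diet value adjusted for that period's pre-diet value, and state in advance which. Use a mixed model with diet, period and sequence as fixed effects and participant as random. For the change, the equivalent is to add period and period × time to the diet × time model. The pre-diet values must stay in: a model of diet, period and sequence fitted to all four visits without time would not target diet-induced change.

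Blocked allocation of the remaining participants is optional. Recruitment began in May 2017 with data collection due to end by February 2018, so it may reach few people.

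Cost: one degree of freedom (19 to 18 for the diet contrast). If there is no period effect, power falls by 85.3 − 83.0 = 2.3 points on average, and by 85.3 − 78.5 = 6.8 points at a 14:6 split.
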